### **5.3.2. Health worker communication assessments + patient exit interviews**

We aim to conduct communication assessments with at least one health worker in each health facility in both the HFI and standard care arms (10 in each arm). Each communication assessment will consist of at least three, and no more than five, health worker/caregiver interaction records. The communication assessments will be conducted immediately before and up to 6 weeks after the HFI training in patient-centered services, and then approximately six months following the training for a total of three cycles. The same health workers will be assessed at each time point to evaluate for changes over time. We will evaluate approximately 20-25 health workers chosen by convenience sampling. Therefore conducting up to 125 health worker/caregiver interactions in each time period; 375 in total, depending on the number of health workers and patients available at the health centers on the days of the study. One health worker will be chosen from each of the level II health centers, and 1-2 health workers will be chosen from each of the level III centers. Exit interviews will be conducted with all consenting caregivers who participated in the assessments, up to a maximum of 125 interviews at each time point, 375 in total.

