Patients to be included in the communication assessments will be 'typical uncomplicated malaria patients'. Inclusion criteria are 1) age: a child under five years of age, 2) fever or suspected fever, and 3) agreement of caregiver to provide informed consent. Exclusion criterion is 1) danger signs of severe disease (Appendix L). The same caregivers will be invited to participate in an exit interview after the consultation (Appendix O). Written informed consent to conduct the assessments, and the exit interviews, will be obtained from caregivers before beginning (Appendix M) as outlined in section 8.2. Demographic information on the caregiver will then be obtained (Appendix N).

The communication assessments will be conducted immediately before and up to 6 weeks after the HFI training in 'improving interactions with patients' and then approximately six months following the training for a total of three cycles. The same health workers will be evaluated in each cycle of the assessments.

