### 6.1. DATA MANAGEMENT

#### 6.1.1. Quantitative data

Quantitative data from the self-filled questionnaires, patient exit interviews, semi-structured questionnaires, structured contextual record, and supply records will be collected by the study team. Data from the paper questionnaires and data collection forms will be entered into an Access database by a data entry clerk and will be double entered to verify accuracy. Back-up files of databases will be stored after each data entry session. For quality control, query programs will be written into the database to limit the entry of incorrect data and ensure entry of data into required fields.

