| 24. Discussion of management of a patient with fever and a negative RDT                    | [ ] |                                                                            | [ ] |

13. What questions or concerns were raised by this group about the training of health workers on fever case management? (Please list)

14. How were each of these concerns addressed, if at all?

15. Which of these concerns do you think were still present at the end of the training?

16. Would you change anything about the fever case management training sessions for clinical staff? If yes, what would you change? How would you change it?

17. Do you have any general comments on this course?

Thank you!

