|                                                                                                                                                                                       | 2 = No                 | [ ] [ ]                |
| 8. How satisfied were you with the treatment you were given? (Allocate category that fits best with response, check with mother)                                        | 1 = Very satisfied     | 3 = Somewhat satisfied |
|                                                                                                                                                                                       | 2 = Satisfied          | 4 = Not satisfied      |
|                                                                                                                                                                                       |                        | [ ] [ ]                |
| Did the health worker explain what this medicine will do?                                                                                                                      | 1 = Yes                | [ ] [ ]                |
|                                                                                                                                                                                       | 2 = No                 | [ ] [ ]                |
| Did the health worker help you to understand how the child should take this medicine?                                                                                          | 1 = Yes                | [ ] [ ]                |
|                                                                                                                                                                                       | 2 = No                 | [ ] [ ]                |
| Did the health worker help you to understand what to expect during the child's illness?                                                                                        | 1 = Yes                | [ ] [ ]                |
|                                                                                                                                                                                       | 2 = No                 | [ ] [ ]                |

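### Appendix O asks about 'this medicine' with Yes/No codes only and never records whether a medicine was given or prescribed, so these two items cannot separate communication from prescribing and stock

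*Supplement*

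**What the plan says.** Appendix O contains two adjacent items on a medicine: "Did the health worker explain what this medicine will do" and "Did the health worker help you to understand how the child should take this medicine". Each offers 1 = Yes and 2 = No and nothing else. The item before them, item 8, asks "How satisfied were you with the treatment you were given" on a four-level satisfaction scale. It does not establish whether any medicine was dispensed or prescribed, and no other item on the form does. There is no skip instruction.

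The form is used for every child in the assessments. Section 5.3.2: "Exit interviews will be conducted with all consenting caregivers who participated in the assessments". Section 5.5 admits "a child under five years of age, 2) fever or suspected fever", subject to consent and no danger signs; receiving a medicine is not a criterion. Both arms are covered, with 10 facilities each.

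Section 7.1 compares categorical exit-interview variables by chi-square or Fisher's exact test at two-sided 0.05 and gives no rule for the denominator. On data entry, section 6.1.1 says that "query programs will be written into the database to limit the entry of incorrect data and ensure entry of data into required fields", without naming which fields are required.

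**The concern.** A question about a medicine that the child did not receive has no correct answer on this form. If the interviewer enters No, the item records absence of a drug as absence of an explanation. If the interviewer leaves it blank, the analyst cannot tell a child without medicine from a skipped question. Either way the right denominator cannot be rebuilt from the form.

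This would matter little if non-receipt were rare and similar in both arms. The intervention gives reasons why it may not be similar. It supplies malaria diagnostics and antimalarials (section 1.2), and its fever training includes "Discussion of management of a patient with fever and a negative RDT" (Appendix E). More RDT-negative children leaving without a drug in the HFI arm would pull these items down there. More stock-outs in the standard care arm would pull them down in that arm. A difference in prescribing or supply could then be read as a difference in communication, or could hide one.

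**Working it through.** **Sample size, from section 5.3.2.** There are 20–25 health workers, with 3–5 interactions each per cycle.
- Maximum: 25 × 5 = 125 per cycle, and 125 × 3 = 375 in total. This reproduces the plan's ceilings.
- Minimum: 20 × 3 = 60 per cycle.
- Split evenly, that is about 62 per arm at most and 30 per arm at least. No power statement exists to reproduce.

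**Assumptions, none of them in the documents.**
- *q*: probability that a medicine is explained, among children who have one; 70%, equal in both arms.
- *s*: share of children with no medicine; 10%, 20% or 30% in one arm against 5% in the other.
- Children without a medicine are entered as No.
- Children are independent. Clustering by health worker is a separate matter.

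**Formula.** Observed Yes rate = *q* × (1 − *s*). With equal communication, the false arm difference is *q* × (*s* in the 5% arm − *s* in the other arm).

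The comparison arm has 0.70 × 0.95 = 66.5%.

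| No medicine | Observed Yes | False difference | p<0.05 at 62 per arm | p<0.05 at 30 per arm |
|---|---|---|---|---|
| 10% v 5% | 0.70 × 0.90 = 63.0% | −3.5 points | 7% | 6% |
| 20% v 5% | 0.70 × 0.80 = 56.0% | −10.5 points | 23% | 13% |
| 30% v 5% | 0.70 × 0.70 = 49.0% | −17.5 points | about 52% | 28% |

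The rejection rates are for the two-sided chi-square test without continuity correction. Exact enumeration for the last row at 62 per arm gives 53%, and a normal approximation 52%. Swapping the arms reverses the sign and leaves the size unchanged.

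**Equal shares.** With *s* = 5% in both arms both rates are 66.5%, the difference is 0 and the test rejects at its nominal 5%.

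**Masking.** Suppose the true explanation rates are 85% (HFI) and 70% (standard care), and 80% and 95% of children have a medicine. The observed rates are 0.85 × 0.80 = 68.0% and 0.70 × 0.95 = 66.5%. A true gain of 15 points appears as 1.5.

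**After the fix.** Restricting to children with a medicine leaves about 62 × 0.90 = 56, 62 × 0.80 = 50 or 62 × 0.70 = 43 against 62 × 0.95 = 59. With *q* equal among them, the expected difference is 0 and rejection returns to about 5%.

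**The case against.** A reader might infer that children without medicine are scored as poor communication. The documents do not support that. No passage says that No is entered for them, the required fields are not named, a paper form can be left blank, and the SOPs promised in section 6.2 are not shown. Nor does Appendix O produce a score. Patient-centred communication is scored from the audio recordings with the MPCC (section 7.2), which this gap does not reach. Only two items of a process evaluation are affected.

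A reader might also equate a negative RDT, or a stock-out, with no medicine. Neither follows. The fever training also covers non-malaria febrile illness, so an RDT-negative child may leave with another drug, and a caregiver told to obtain a drug elsewhere can still have it explained. Nothing in the documents supports a 30% share without medicine, and the 52% figure needs both that share and the maximum sample.

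Finally, the consultations are recorded, so receipt might be checked from the recordings. No such linkage is planned for these items.

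These points limit the size and certainty of the bias. They do not answer the gap in the form: whatever SOP or coding habit applies, Appendix O holds no record of receipt. It does not look like house style either, since Appendix E carries an N/A code and Appendix U uses skips and codes for don't know and refused.

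**Conclusion.** The point holds as a fault in two items of one form. As written, they mix communication with prescribing and stock, and the denominator that would separate them is not collected on the form. Whether this biases the arm comparison, and in which direction, depends on shares and coding that the documents do not give. Under the stated assumptions the false difference runs from 3.5 to 17.5 points, and the chance of a spurious significant result from 7% to about 52% at 62 per arm, or 6% to 28% at 30 per arm. At the mild end this is close to nominal, and with equal shares it vanishes. No ACT PRIME outcome in Table 1.1 is shown to depend on these items. The case for acting is that the repair is cheap and that receipt not asked at the interview cannot be recovered from the form later.

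**What to change.** Insert before the two items: *Was the child given or prescribed any medicine today? 1 = Given, 2 = Prescribed but not given, 3 = None.* Add a not-applicable code to the two medicine items only, with a skip to it when the answer is 3. State in section 7.1 that these two items are analysed among children given or prescribed a medicine, and report that proportion by arm and cycle beside them. Note there that this subset is defined after randomisation and may itself be shaped by the intervention, so the restricted comparison is descriptive of communication among recipients and not a fully protected randomised contrast.

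Keep item 8 (satisfaction with treatment) for all caregivers. Dissatisfaction among those sent home without a medicine is a genuine result and belongs to the interview's stated purpose. It may be reported by receipt as well.

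The cost is one added question, one code on two items, a skip rule in the database and slightly smaller denominators for the two items.

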## APPENDIX Q: IDI DATA COLLECTION TOOL

### HFI IMPLEMENTERS

|                                                                                                                                                                     |                                                                                                                                                                                                                                                                                                                                                                                                      |
|---------------------------------------------------------------------------------------------------------------------------------------------------------------------|------------------------------------------------------------------------------------------------------------------------------------------------------------------------------------------------------------------------------------------------------------------------------------------------------------------------------------------------------------------------------------------------------|
| Study ID

                                                         | Date

 

 

 
 
 day month year 
 |
| Position:
1 = Study coordinator
2 = Medical Officer
3 = Trainer
4 = Community Health worker
5 = Clinical officer
6 = Laboratory technician | 7 = Laboratory Assistant
8 = Home Visitor
9 = Implementation support (administration, logistics, procurement, research assistant)
10 = Other _____

                                                                                                                                            |

### DEMOGRAPHIC INFORMATION

|                                                                                                                                                          |                                                                                                                                                                                                                                                                                                                                                                                                             |
|----------------------------------------------------------------------------------------------------------------------------------------------------------|-------------------------------------------------------------------------------------------------------------------------------------------------------------------------------------------------------------------------------------------------------------------------------------------------------------------------------------------------------------------------------------------------------------|
| 1. Age
Years 

                                    | 5. Highest level of education or qualification achieved

 
 0 = None
 1 = Primary (P1 — P7)
 2 = Secondary (S1 — S6)
 3 = Certificate
 77 = Other _____ 
 
 4 = Diploma
 5 = Bachelor's degree
 88 = Don't know
 99 = Refused to answer 
 
 |
| 2. Gender
1 = Male 

2 = Female                | 

                                                                                                                                                                                                                                                                                                                  |
| 3. Originally from this area?
1 = Yes
2 = No 

 | 

                                                                                                                                                                                                                                                                                                                  |
| 4. Number of years worked in this job

           | 6. Year graduated

                                                                                                                                                                                                                                                                                 |

### PART 1: INTRODUCTION

Conduct the interview according to the directions below and record information as indicated.

#### Introduction to in-depth interview

*“Hello, my name is ..... I am interested in interviewing you. I would like you to express your own views and experiences about your perspectives on the implementation of the ACT PRIME health facility intervention to improve the health of children in Tororo by improving services at government-run health facilities. A note-taker will be writing down what you say for our records, and we will record the interview using a digital recorder; these notes will be kept securely and your name will not be used anywhere. Your answers will be looked at together with those of many other implementers and you will not be identifiable in any reports that are published.*

*It is very important for us to hear your views and experiences because you have experience implementing the intervention and can give us this insight. We hope you will have time to spend with us now to complete this interview. The interview will take about 45 minutes; but if you prefer we can reschedule the interview for tomorrow or another day of your convenience.*

*Do you have any questions? Do you agree to continue before we start?*

*Now we request that we all switch off our mobile phones so that we are not distracted.”*

**PART 2: IMPLEMENTER IN-DEPTH INTERVIEW (2)**

**Domains, topic questions, and probes:** Use the table below to help you administer the questions during the interview.

| Domain                                     | Topic and Probes                                                                                                                                                                                                                                                                                                                                                                                                                                                                                                                                                                                                                                                                                                                                                                             |
|--------------------------------------------|----------------------------------------------------------------------------------------------------------------------------------------------------------------------------------------------------------------------------------------------------------------------------------------------------------------------------------------------------------------------------------------------------------------------------------------------------------------------------------------------------------------------------------------------------------------------------------------------------------------------------------------------------------------------------------------------------------------------------------------------------------------------------------------------|
| 1. Role of the implementer          | a) What has been your role as an implementer of this intervention?                                                                                                                                                                                                                                                                                                                                                                                                                                                                                                                                                                                                                                                                                                                           |
| 2. Meeting participant expectations | 
a) What do you think participants expected from the health facility intervention?
 
b) Do you think this intervention met their expectations? Probe: What expectations were met and what else happened that you think they were not expecting?
                                                                                                                                                                                                                                                                                                                                                                                                                                                                                                                            |
| 3. Implementation Process           | 
a) In your opinion, was the training component of the HFI implemented as planned? Probe for specifics, why?
 
b) In your opinion, was the information management component of the HFI implemented as planned? Probe for specifics, why?
 
c) In your opinion, was the supply of consumables including malaria diagnostics and antimalarial drugs component of the HFI implemented as planned? Probe for specifics, why?
 
d) Looking back over the past two years, what component of the intervention do you think was most successfully implemented? Probe for specifics.
 
e) Looking back over the past two years, what component of the intervention do you think was least successfully implemented? Probe for specifics.
 |

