| Study Design         | ACT PROCESS consists of a comprehensive evaluation framework to evaluate the process, context and impact of the ACT PRIME intervention. The evaluation framework includes: 1) a logic model to detail the components, effects and intended outcomes of the HFI; 2) a process evaluation to document the implementation of the HFI activities from the perspective of implementers, health workers, community members, and key stakeholders; 3) a context evaluation to capture information on factors that may have affected the HFI implementation or outcomes; and 4) an impact evaluation to assess the wider impact of the HFI beyond outcomes of the ACT PRIME study. These evaluation components will be assessed using self-filled questionnaires, health worker communication assessments and patient exit interviews, in-depth interviews and semi-structured questionnaires, focus group discussions, and a structured contextual record.                                                          |
| Study site           | In Tororo District, the five sub-counties of West Budama North Health Sub-district (Nagongera, Paya, Kirewa, Kisoko, and Petta), and two sub-counties of West Budama South Health Sub-district (Mulanda and Rubongi) will be included.                                                                                                                                                                                                                                                                                                                                                                                                                                                                                                                                                                                                                                                                                                                                                                       |

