### 3.2. SECONDARY OBJECTIVES

1. To develop a comprehensive logic model of the ACT PRIME HFI with intervention components mapped through to their intended effects and outcomes.
2. To evaluate the process of the HFI implementation including health worker training, health center management tools, supply of AL and RDTs for malaria, and interactions with local and district stakeholders.
3. To develop a rich contextual record of factors that may have affected the HFI implementation outcomes such as other interventions or programmes implemented in the area, changes to malaria case management guidelines, and other environmental, economic, political or individual factors.
4. To assess the wider expected and unexpected impacts of the HFI at the household, community, private sector, and public health system levels.

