### 4.3. PROCESS EVALUATION

The process evaluation will involve two lines of research, (1) documentation of the implementation of the intervention as delivered by the study team and (2) qualitative study of the functioning and interpretation of the intervention by implementers and recipients. As outlined in Figure 4.1, we will be evaluating four aspects of the HFI including (1) health worker training modules, (2) health center management tools, (3) supply of AL and RDTs for malaria, and (4) interaction with the district regarding staffing and drug stocks.

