#### 4.3.1. Documentation of implementation

The logic model will be used to identify relevant activities for the process evaluation. For each activity, the following evaluation criteria will be used as categories of assessment [37].

- Fidelity (quality)                      The extent to which the intervention was implemented as planned
- Dose delivered (completeness)      Amount or number of intended units of each intervention or component delivered or provided by interventionists
- Dose received (exposure)            Extent to which participants actively engage with, interact with, are receptive to and/or use materials or recommended resources. Can include 'initial use' and 'continued use'

- Reach (participation rate) Proportion of the intended priority audience that participates in the intervention; often measured by attendance; includes documentation of barriers to participation
- Recruitment Procedures used to approach and attract participants at individual or organizational levels; includes maintenance of participant involvement in intervention
- Context Aspects of the environment that may influence intervention implementation or study outcomes; includes contamination

Variables for data collection for each activity are formulated under each of the above headings by analysing the materials used for the HFI implementation including:

- Training packages: Health center management training; Training in fever case management and use of RDTs, Training in patient-centered services.
- Management tools: PHC Fund Accounting Tool, ACT Drug Distribution Assessment Tool
- Supply of AL and RDTs: drug stock cards, requisition and issue vouchers from health centers and the health sub-district records
- District and health sub-district interactions: Logs documenting interactions with district, health sub-district, and health center staff.

We will capture information on these variables during the implementation and monitoring and evaluation of the HFI using monthly health center records, health worker training evaluation self-filled questionnaires, IDIs with health workers and FGDs with primary caregivers. The data captured will be linked with other quantitative outcome data collected through ACT PRIME using unique identifiers of health center, community or individual health worker or intervention participant.

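### The implementer interview guide has no question on district interaction, one of the four aspects of the process evaluation, and Table 4.1 leaves stakeholder interviews out of that evaluation

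*Supplement*

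**What the plan says.** Section 4.3 sets the scope of the process evaluation: "we will be evaluating four aspects of the HFI including (1) health worker training modules, (2) health center management tools", followed by "3) supply of AL and RDTs for malaria, and (4) interaction with the district regarding staffing and drug stocks". Secondary objective 2 matches this after training: "health center management tools, supply of AL and RDTs for malaria, and interactions with local and district stakeholders". Section 4.3.1 defines fidelity as "The extent to which the intervention was implemented as planned".

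Section 5.6 invites implementers who delivered training, worked on drug distribution, or dealt substantially with health workers or with district or local officials. Up to five will be interviewed with the pre-defined guide in Appendix Q. Table 4.1 marks these interviews for process, context and impact.

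Domain 3 of Appendix Q asks whether three things went as planned: training (3a), information management (3b: "In your opinion, was the information management component of the HFI implemented as planned") and supply of consumables (3c). Items 3d and 3e ask which component was most and least successfully implemented. Item 5a asks whether the tools were taken up in practice.

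On stakeholders, the synopsis says that implementation will be documented "from the perspective of implementers, health workers, community members, and key stakeholders". The Rationale names only implementers, health workers and community members for the process evaluation. Table 4.1 marks stakeholders for context and impact only.

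**The concern.** The list of components in Appendix Q domain 3 is not the list in section 4.3. The element that drops out completely is district interaction. Some implementers are chosen because they carried it out, but the guide never raises it with them.

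The primary objective is to learn why the intervention worked or did not. Suppose staffing or drug stocks fail to improve. The process evaluation should then separate two explanations: the planned engagement with the district was not delivered, or it was delivered and had no effect. Implementers are well placed to say which, and to give reasons. If they are not asked at 9-12 months after roll-out, their account cannot be recovered later.

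The Table 4.1 point is related. Stakeholders are the other side of the same interaction, and their answers on staffing and re-stocking are formally assigned to context and impact, not to process.

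**Working it through.** No arithmetic beyond counting applies. The check sets the four aspects of section 4.3 against every question in Appendix Q, and then looks for the same content in the other instruments.

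| Aspect (section 4.3) | Appendix Q | Elsewhere |
|---|---|---|
| 1. Training modules | 3a and domain 4 | Trainer and participant questionnaires (Appendices C-H) |
| 2. Management tools | Uptake only (5a) | Appendix C trainer questionnaires; Appendix R; Appendix U Part 2, items 3-8 |
| 3. Supply of AL and RDTs | 3c | Stock cards and vouchers (5.10, Appendix BB) |
| 4. District interaction | No item | Interaction logs (4.3.1); Appendix S 1c, 3a-b, 6b; Appendix R on staffing and re-stocking; Appendix U section 7, item 8; sub-district supply records |

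**Row 2.** Section 4.3.1 identifies the tools: "Management tools: PHC Fund Accounting Tool, ACT Drug Distribution Assessment Tool". Appendix Q asks about their uptake. The Appendix C trainer questionnaires ask whether teaching and materials went as planned for budgeting and accounting (HCM01), and for the stock card, the voucher and the ADDAT (HCM02). Trainers count as implementers under section 5.6. So people who delivered this aspect are asked about its fidelity, and close to the time of delivery.

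**Row 4.** No Appendix Q item names the district. The open items (1a on role, 3d, 3e, 7c on other influences, and the closing question) could bring it up, but none prompts for it. Taking the other sources in turn:

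- Logs document that interactions took place.
- Appendix S asks stakeholders about their involvement, about actions on staffing, about changes in re-stocking, and about the level of district support.
- Appendix R asks health workers what changed in staffing and re-stocking and what challenges remain.
- Supply records show orders and receipts.

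These sources cover the result and much of the activity. None asks the delivering team whether its planned engagement was carried out, or why it was or was not.

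**Counts.** Aspects with no prompt in Appendix Q: 1 of 4. Interviews affected: up to 5. In-depth interviews: 5 implementers + 10 health workers + 10 stakeholders = up to 25, of which 5 + 10 = 15 carry a process mark and 10 do not.

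**The case against.** The strongest case against has four parts.

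1. Section 4.3.1 does not list implementer interviews among its sources on implementation. It lists health center records, training questionnaires, health worker interviews and caregiver discussions, and gives logs for the district element. This is correct, and it lowers the weight of the point. But section 4.3 also plans a qualitative study of how the intervention functioned for implementers and recipients, Table 4.1 marks implementer interviews for process, and domain 3 of the guide does ask about fidelity. Having taken on that task, it omits one aspect.
2. Section 1.2 gives the intervention three components, and district interaction is not one of them. True, but section 4.3 and objective 2 commit this study to evaluating it.
3. These are open topic-guide questions, and an implementer whose work lay with the district may raise it unprompted. Possible, but with at most five interviews it is not something to rely on.
4. The missing stakeholder mark does not stop their answers being collected or used, and Table 4.1 agrees with the Rationale. Both are true; the synopsis is the passage that differs. The documents still need to agree.

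A reader might go further and infer that fidelity of the management tools is also never asked of those who delivered them. The Appendix C trainer questionnaires rule that out. Nor is item 3b simply misplaced: the introduction to Appendix R lists information management as a separate study activity. A reader might also infer that only the logs and the one Appendix U agreement item on district communication remain, so that the study could not tell non-delivery from failure. The sources in row 4 of the table do not support that.

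**Conclusion.** The point holds in a narrow form. One of the four aspects of the process evaluation is not prompted in the up to five implementer interviews. The up to 10 stakeholder interviews that bear on it have no process mark, contrary to the synopsis. Objective 2 can still be addressed from other sources. What is missing is a prompted account from the delivering team of whether district engagement went as planned, and the reasons.

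This is a cheap improvement, not a flaw that threatens the study's conclusions. The conclusion assumes that interviewers follow Appendix Q as printed and do not add the topic themselves, and that the logs record contacts more than reasons; their format is not shown.

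**What to change.** - In Appendix Q domain 3, add an item in the style of 3a-3c: *Was the interaction with the district and health sub-district over staffing and drug stocks implemented as planned? Probe for specifics, why?* Place it before 3d and 3e, so that the most/least successful items follow a list that includes it.
- Reconcile the synopsis, the Rationale and Table 4.1 by marking key stakeholders for the process evaluation, and code the Appendix S domain 3 answers under process.

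Cost: one added question in a 45-minute interview, a few more minutes in up to five interviews; one mark in Table 4.1 and a matching phrase in the Rationale; and some extra coding of answers that will be collected anyway. The change has to be made before the interviews begin.
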